### 8.1 Prohibited Medications

Subjects should not receive any approved medications with antitumor effects during the treatment period, such as chemotherapy, traditional Chinese medicine, and immunoregulator (thymosin, interferon, interleukin-2, purple dragon, lentinan, etc.).

Subjects should not receive live vaccines from 14 days before the first dosing of the study treatment to 60 days after the last dosing, including measles, mumps, rubella, chickenpox, yellow fever, seasonal influenza, H1N1 influenza, rabies, Bacille Calmette-Guerin vaccine (BCG), and typhoid vaccines.

### 8.2 Medications Given Cautiously

**Medications/food that affect anlotinib will be used cautiously:**

- Anticoagulant or clot-preventing medications, including but not limited to: Salicylic acid derivatives (e.g., aspirin); heparins (e.g., low molecular weight heparin, enoxaparin, dalteparin sodium, ardeparin sodium, etc.); Preventive anticoagulant drugs after cardiovascular events (e.g., clopidogrel and ticagrelor);
- Medications that interfere with hepatic cytochrome P450 enzymes, including but not limited to CYP3A inducers (carbamazepine, rifampicin); phenobarbital inhibitors (ketoconazole, itraconazole, erythromycin, and clarithromycin); CYP3A4 substrate (simvastatin, cyclosporine,

and piperidine); other medications metabolized by CYP3A4 (benzodiazepines, dihydropyridine calcium antagonist [calcium antagonism may be selected as appropriate for uncontrolled ACEI hypertension]; HMG-CoA reductase inhibitor); CYP2C9 substrate (diclofenac, phenytoin sodium, piroxicam, S-warfarin, and tolbutamide); CYP2C19 substrate (diazepam, imipramine, lansoprazole, and S-mephenytoin);

- Citrus, star fruit, grapefruit, and grapefruit juice;
- Medications that prolong the cardiac QTc, including but not limited to:
  - ✓ Antimicrobials (clarithromycin, azithromycin, erythromycin, roxithromycin, metronidazole, moxifloxacin);
  - ✓ Antiarrhythmic drugs (quinidine, sotalol, amiodarone, disopyramide, procaine amide);
  - ✓ Antipsychotics (risperidone, fluphenazine, haloperidol, thioridazine, pimozide, olanzapine, clozapine);
  - ✓ Antifungal drugs (fluconazole, ketoconazole);
  - ✓ Antimalarial drugs (mefloquine, chloroquine);
  - ✓ Antidepressants (amitriptyline, imipramine, clomipramine, dosulepin, doxepin).

### 8.3 Permitted Concomitant Medications/Treatments

All treatments that the investigator considers no effects on study endpoints may be administered, such as unconventional therapies (e.g., herbal or acupuncture) and vitamin/mineral supplements.

Bisphosphonates are allowed for subjects with bone metastases during the trial. Palliative radiation therapy in a small area (<5% bone marrow region) will be allowed for subjects with uncontrolled pain of bone metastases after systemic therapy or topical analgesia.

To prevent an infusion reaction of TQB2450, H1 blockers (Diphenhydramine 50 mg, IV or equivalent) and acetaminophen (500-650 mg, oral or IV) may be premedicated 30 to 60 minutes prior to infusion of TQB2450. Systemic corticosteroid therapy for the management of infusion reactions or irAEs should be reduced gradually for at least 4 weeks. The reduced dose would not suppress immune system function (prednisone or equivalent  $\leq 10$  mg/day).

## 9. Efficacy Evaluation

Since similar drugs of TQB2450 induced pseudo-progression in the clinical administration, the efficacy evaluation will be assessed by RECIST v1.1 and further confirmed by iRECIST criteria. That is, patients identified as having disease progression as per RECIST v1.1 will be confirmed by iRECIST to determine further treatment.

Efficacy will be assessed every 2 cycles from cycle 1 day 1 until the radiologically confirmed disease progression. The frequency of radiographic assessments is independent of dose delays and/or dose interruptions. For subjects who discontinue the study drug for reasons other than disease progression, the tumor assessment will still be conducted every 2 cycles until starting a new antitumor therapy, disease progression, withdrawal of consent, or death, whichever occurs first.

The methods of radiographic assessment (CT or MRI) will be determined by the investigator. However, the assessment methods, machines, and technical parameters should be consistent throughout the study period. Contrast media is required for subjects without contraindications. For subjects who had received a radiographic assessment within 14 days before the first dose using the same procedure in the same center, the radiographic assessment could be used as the baseline data in this trial. The baseline tumor assessment should include enhanced CT or MRI of the chest, abdomen, and pelvis (except for subjects with an allergy to contrast media). During the screening period, a cranial plain scan plus enhanced MRI, and bone scan is required for all subjects. However, for subjects without bone metastases, whether the bone scan is performed will be decided by the investigator according to the symptoms. All suspected lesions will be evaluated by imaging. For subjects with bone metastases, the lesions will be monitored using a bone scan. If there is no exacerbation of clinical symptoms in these subjects, re-examination is not required at each visit for tumor assessment; otherwise, a timely re-examination is necessary. An unplanned tumor evaluation should be performed for subjects with suspected disease progression before the next planned evaluation. The radiographic assessment will only be conducted for lesions, but suspected lesions will also be evaluated by imaging.

## **10. Safety Analysis**

### **10.1 AEs**

AEs are defined as any untoward medical occurrence in a patient or clinical investigation subject administered a pharmaceutical product and which does not necessarily have to have a causal relationship with this treatment. Thus, AEs could be any unfavorable and unintended sign (including an abnormal laboratory finding), symptom, or disease temporarily associated with the use of a medical treatment or procedure regardless of whether it is considered related.

AEs also include the complications resulting from the protocol-defined interventions, such as complications caused by tissue biopsy or other invasive procedures; and the worsening of underlying disease (except for tumor progression) assessed by the investigator(s) during the reporting period of AEs.

Investigator(s) are required to record any AEs in subjects, including the events, AEs-related symptoms, time of occurrence, severity, duration, management, and outcomes.

### **10.2 AEs Grade**

The severity grade of any AEs will be assessed according to the definitions in NCI-CTCAE v5.0.

### **10.3 Record of AEs**

During the reporting period of AEs, the investigator(s) are required to record any AEs, including SAEs, in the CRF/eCRF. For the report of AEs, the investigator(s) are required to use the correctly standardized medical terminology rather than colloquialism and abbreviations. The start date, severity grade as per NCI-CTCAE v5.0, stop date, causality to study drugs, effects on the trial, concomitant therapy, and recovery will be recorded.

### **Diagnosis vs. signs and symptoms**

A diagnosis (if known) should be recorded on the CRF/eCRF rather than individual signs and

symptoms (e.g., record only liver failure or hepatitis rather than jaundice, asterixis, and elevated transaminases). However, if a constellation of signs and/or symptoms cannot be medically characterized as a single diagnosis or syndrome at the time of reporting, each event should be recorded on the CRF/eCRF as AEs. If a diagnosis is subsequently established, all previously reported AEs based on signs and symptoms should be nullified and replaced by 1 AE report based on the single diagnosis.

#### **AEs occurring secondary to other events**

In general, AEs occurring secondary to other events (e.g., cascade events or clinical sequelae) should be identified by their primary cause, except for severe or serious secondary events. However, medically significant AEs occurring secondary to an initiating event that are separated in time should be recorded as independent events on the CRF/eCRF. All AEs should be recorded separately as primary or secondary events if it is unclear as to whether the events are associated.

#### **Persistent, intermittent, or single AEs**

Persistent AE extends continuously, without resolution between cycles/courses, such as the upper respiratory tract infection lasting 5 days. The event must only be reported once unless the grade becomes more severe. For severity grade, the highest severity grade should be recorded.

Intermittent AE occurs and resolves during a cycle/course of therapy, but without clinically significant outcomes, such as nausea and vomiting lasting for several days with the intermittent resolution, and persistent hypertension with intermittent resolution. The event must only be reported once. For severity grade, the highest severity grade should be recorded.

Single AE is one that occurs independently or only once during therapy, such as falls and one vomiting event during the trial. The event must only be reported once.

It should be noted that these above events are recurrent after clinically significant resolution and meanwhile have no course continuity with the former, each recurrence of an AE should be recorded separately on the CRF/eCRF.

#### **Abnormal laboratory tests or vital signs**

Laboratory test results will be recorded on the laboratory results pages of CRF. Not all abnormal laboratory tests and vital signs will be reported as AEs. Investigator(s) have the responsibility to review all laboratory findings and vital signs. Medical and scientific judgment should be exercised in deciding whether an isolated laboratory abnormality should be classified as an AE. Any abnormalities that meet one or more of the following conditions for clinical significance will be reported as AEs:

- Accompanied by clinical symptoms;
- Leading to a treatment change (e.g., dose modification, interruption, or discontinuation);
- Requiring medical intervention or the change of concomitant therapy (e.g., concomitant medication, new treatment, treatment interruption, discontinuation, or any other change);
- Have significant clinical significance as judged by the investigator.

If a clinically significant laboratory abnormality is a sign of a disease or syndrome (e.g., increased ALT/AST and bilirubin caused by hepatic dysfunction), only the diagnosis should be recorded on the CRF/eCRF (hepatic dysfunction). Otherwise, the abnormality should be recorded along with a descriptor indicating if the test result is above or below the normal range. If the abnormalities have corresponding standard clinical terms, the standard clinical terms should be recorded (e.g., an increase in blood potassium to 7.0 mmol/L should be recorded as hyperkalemia).

### **Death**

For reporting death events, the death due to AE should be recorded as the single medical concept on the CRF/eCRF and reported as SAE. If the cause of death is unknown, “unexplained death” should be recorded on the CRF/eCRF, reported as SAE provisionally, and confirmed by further investigation. If the cause of death later becomes available, the “unexplained death” should be replaced by the established cause of death.

### **Pre-existing medical conditions**

A preexisting medical condition should be recorded as an AE only if the frequency, severity, or character of the condition worsens during the study. When recording such events, it is important to convey the concept that the preexisting condition has changed by including applicable descriptors (e.g., more frequent headaches, and aggravated hypertension).

### **Hospitalization or prolongation of existing hospitalization**

The following conditions leading to hospitalization or prolongation of existing hospitalization are not classified as SAEs:

- The hospitalization or prolongation of existing hospitalization required by protocol (e.g., administration and efficacy evaluation);
- An elective hospitalization for a pre-existing condition unrelated to the study indication. For example, the planned surgery or treatment before study or the scheduled surgery or treatment after enrollment. However, hospitalization for surgery or treatment due to disease worsening (surgery or treatment in advance) will be classified as SAEs.

### **Surgery**

If the disease for surgery is definite, the disease should be recorded as AE rather than surgery (e.g., for subjects who underwent inguinal herniorrhaphy, AE is inguinal hernia rather than inguinal herniorrhaphy). Otherwise, the surgery should be recorded as AE (e.g., for subjects who underwent abbreviated laparotomy, abbreviated laparotomy is AE).

### **Pregnancy**

If a female subject or a female partner(s) of a male subject becomes pregnant during the trial, the investigator(s) should be informed immediately. Investigator(s) are required to report to the sponsor within 24 hours of learning of its occurrence. Pregnant subjects should immediately stop using the study drug. The investigator should counsel the patient, and discuss the risks of continuing the pregnancy and the possible effects on the fetus. Pregnant subjects will be monitored until the end of pregnancy. All pregnancies within 30 days of the last administration will be reported to the

investigator(s).

Both induced and spontaneous abortions should be reported as SAEs. Any congenital anomalies/birth defects in infants born to female subjects or female partners of male subjects who had taken study drugs should be reported as SAEs.

### **Disease progression**

If the observed progression is confirmed to be consistent with the expected pattern of primary tumor progression, it will not be considered an AE. The hospitalization due to this progression will also not be considered an SAE. If symptoms cannot be confirmed to be caused by tumor progression, or consistent with the expected pattern, the events will be considered an AE or an SAE.

### **10.4 Follow-up of AEs**

Investigator(s) are required to follow up all AEs until any of the following occurs:

- AEs resolve to baseline;
- No further remission will be expected by the investigator(s);
- Death;
- Lost to follow-up;
- AEs that are not related to the study treatment confirmed by the investigator(s);
- Starting new antitumor treatment;
- End of clinical or safety data collection, or the database lock;
- No clinical or safety data are collected, or the database is eventually closed.

The outcomes of each AE (including the date of resolution and death) need to be recorded in the CRF/eCRF.

### **10.5 Causality to Study Drugs**

Investigator(s) are required to assess the causality of AEs to study drugs, according to the following 5 criteria:

- (1) Whether the administration time and the suspected AEs exhibit a reasonable relationship;
- (2) Whether the suspected AEs fulfill the criteria for the typical reactions of the drug;
- (3) Whether the suspected AEs can be explained by the effects of the combined drug, patient's clinical condition, or other therapies;
- (4) Whether the suspected AEs disappear or are mitigated after drug discontinuation;
- (5) Whether the same AEs recurred after repetitive administration of the study drugs.

|          | 1 | 2 | 3 | 4 | 5 |
|----------|---|---|---|---|---|
| Definite | + | + | - | + | + |

|           |   |   |   |   |   |
|-----------|---|---|---|---|---|
| Probable  | + | + | - | + | ? |
| Possible  | + | + | ± | ± | ? |
| Unlikely  | + | - | ± | ± | ? |
| Unrelated | - | - | + | - | - |

Note: +, Yes; -, No; ±, probably Yes or No; ?, unknown.

AEs will be calculated as the sum of definitely-related, probably-related, and possibly-related events.

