**Emergency unblinding for pharmacovigilance**

In the case of SUSAR, the independent pharmacovigil commissioners shall apply for the blinding code to the system manager. The system manager will directly send the blinding code to the pharmacovigil commissioners who shall be responsible for keeping and maintaining the blinding code.

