## 10.7 Management of SAEs

Any SAE, whether or not related to the study drug, occurring must provide the written report to the sponsor or their representative ([contact]) within 24 hours of being aware of its occurrence, followed by the written follow-up report in detail. For death events, the investigator(s) have to provide the documents (e.g., autopsy and medical report) to the sponsor and ethics committee. The sponsor is required to immediately assess the severity of SAEs, their causality to the study drug, and whether it is an expected event. For suspected unexpected SAEs, the sponsor should quickly report to all participating investigators, clinical trial institutions, and the ethics committee, as well as the Drug Administration; Investigators are also required to inform these suspected unexpected SAEs of the ethics committee.

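### Section 10.5 makes being a typical reaction of the drug a condition for any related rating, so investigators must rate atypical events Unlikely at most and the treatment-related tables miss them

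*Protocol*

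**What the plan says.** Section 10.5 gives the task to the sites: "Investigator(s) are required to assess the causality of AEs to study drugs, according to the following 5 criteria". Criterion 1 is timing, criterion 2 is "Whether the suspected AEs fulfill the criteria for the typical reactions of the drug", criterion 3 is whether something else explains the event, criterion 4 is improvement on stopping, and criterion 5 is recurrence on re-exposure. A table assigns codes to five ratings, with the key "Note: +, Yes; -, No; ±, probably Yes or No; ?, unknown". The section closes with "AEs will be calculated as the sum of definitely-related, probably-related, and possibly-related events".

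Three other sections bear on this:

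- Section 10.7 sends all serious events to the sponsor: "Any SAE, whether or not related to the study drug, occurring must provide the written report to the sponsor". The sponsor then judges severity, causality and expectedness. It adds: "For suspected unexpected SAEs, the sponsor should quickly report to all participating investigators".
- Section 4.4.3 (emergency unblinding for pharmacovigilance) provides: "In the case of SUSAR, the independent pharmacovigil commissioners shall apply for the blinding code".
- Section 13.5.2 tabulates all AEs and TEAEs, and separately treatment-related TEAEs and treatment-related SAEs. Fisher's exact test compares arms when necessary.

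**The concern.** Whether a drug caused an event and whether the event was already known are two questions. Section 10.7 keeps them apart. The investigator table joins them, because resemblance to the drug's typical reactions becomes a precondition for calling an event related. Evidence from timing, stopping and re-exposure cannot make up for its absence.

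At stake are the treatment-related TEAE and SAE summaries. A genuinely new toxicity of the four-drug regimen would be undercounted there, and more so in the arm that causes it. That would understate the difference between arms in those tables.

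The closing sentence adds a smaller problem. Read literally, it limits AEs to related events. That conflicts with section 10.1, where an AE needs no causal link, and with the separate listing of all AEs in section 13.5.2.

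**Working it through.** **The table in section 10.5**

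| Rating | 1 timing | 2 typical | 3 other cause | 4 stopping | 5 re-exposure |
|---|---|---|---|---|---|
| Definite | + | + | - | + | + |
| Probable | + | + | - | + | ? |
| Possible | + | + | ± | ± | ? |
| Unlikely | + | - | ± | ± | ? |
| Unrelated | - | - | + | - | - |

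The flexible code ± is used for criteria 3 and 4 but never for criterion 2. Possible and Unlikely differ in that one cell.

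**Enumeration.** Let criteria 1 to 4 be answered + or -, and criterion 5 be +, - or unknown. That gives 2 × 2 × 2 × 2 × 3 = 48 patterns, 24 of them with - on criterion 2. I let ± accept either answer. The code ? can be read strictly (unknown only) or loosely (any answer).

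For the 24 atypical patterns:

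- *Strict:* Unlikely takes 1 × 2 × 2 × 1 = 4 and Unrelated takes 1. So 5 are not related, 24 - 5 = 19 fit no row, and 0 are related.
- *Loose:* Unlikely takes 1 × 2 × 2 × 3 = 12 and Unrelated takes 1. So 13 are not related, 24 - 13 = 11 fit no row, and 0 are related.

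For the 24 typical patterns:

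- *Strict:* Possible takes 4 (Probable's one pattern lies within them) and Definite adds 1, so 5 are related.
- *Loose:* Possible takes 12, including those of Definite and Probable, so 12 are related.

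**Two cases.** Take an event with plausible timing, not typical, no other cause, that resolves on stopping.

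- Re-exposure unknown: Unlikely on both readings.
- Recurrence on re-exposure: Unlikely on the loose reading, no row on the strict one.

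**Ceiling from the reported results.** Supplementary Table S3 gives patients with TEAEs and with TRAEs. The number with a TEAE but no TRAE in a row is the most that any change of rating could move in that row. Arms are in the order four-drug, anlotinib plus EC, EC alone.

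- Any grade: 246 - 246 = 0; 244 - 243 = 1; 246 - 245 = 1.
- Grade 3 or more: 232 - 229 = 3; 234 - 230 = 4; 219 - 214 = 5.
- Leading to death: 26 - 11 = 15; 15 - 6 = 9; 17 - 4 = 13.

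This assumes that TRAEs in Table S3 are the three related ratings of section 10.5. These are ceilings, not estimates: nothing shows how many ratings turned on criterion 2. For deaths the ceiling is generous, since section 10.6 also has deaths from disease progression reported as SAEs. Counts for single preferred terms could shift more than these per-patient totals.

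**The case against.** The strongest reply is that safety detection does not depend on this table. Every SAE reaches the sponsor within 24 hours whatever its rating. The sponsor assesses causality and, separately, expectedness, and nothing ties it to the investigators' scale. All AEs, TEAEs, events of grade 3 or more, discontinuations and deaths are tabulated by arm without regard to causality, in a randomised, blinded, placebo-controlled trial with iDMC safety review. A new toxicity would show as an imbalance. All of this stands and limits the seriousness of the point.

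It also rules out several stronger readings that a reader might infer:

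- *That no SUSAR can arise.* The sponsor can identify one under section 10.7. Nor does the protocol equate typical with expected: an event of a typical kind may still be unexpected, for example in severity.
- *That such events are filed as Unrelated and their follow-up ends.* With plausible timing the row is Unlikely; Unrelated needs a no on timing. Section 10.4 ends follow-up for events confirmed as not related and does not say that Unlikely suffices.
- *That the problem can be sized from the 33 phase I patients in section 1.6.* Typical is not defined as seen in those patients. The protocol also draws on knowledge of similar drugs, and section 1.10 summarises 1576 patients given anlotinib.

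On the closing sentence, the reply is that a qualifier was simply lost. Section 13.1 names AEs and adverse reactions separately, and Table S3 reports TEAEs and TRAEs separately, so the literal reading was evidently not applied. That is fair, but the sentence is still wrong as printed.

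None of this answers the core point. An investigator who follows the table cannot count an atypical event as treatment-related.

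**Conclusion.** The point holds for investigator ratings and what is built on them. Typicality is a necessary condition for a related rating: 0 of 24 atypical patterns qualify on either reading of the unknown code. Atypical events are therefore undercounted in the treatment-related TEAE and SAE tables. For atypical serious events, SUSAR detection rests on the sponsor's assessment alone, for which section 10.7 states no criteria. Atypical non-serious events have no second causality assessment, although they remain in the all-event tables. Section 10.5 needs to be reconciled with sections 4.4.3 and 10.7.

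The number of events affected cannot be derived. At patient level, Table S3 caps any shift in grade 3 or more TRAEs at 3, 4 and 5 patients in the three arms. The conclusion assumes that investigators apply the table as printed. It is a moderate defect in a secondary safety summary and cheap to correct. It does not block SAE reporting or affect PFS or OS.

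**What to change.** 1. In the Possible row, change criterion 2 from + to ±.
2. In the Unlikely row, change criterion 3 from ± to +. Without this, the printed Unlikely row would fall wholly inside the new Possible row. Since ± on criterion 3 in the Possible row also admits a yes, add a line that an atypical event with a clear alternative explanation takes Unlikely. Of the four atypical patterns with plausible timing and unknown re-exposure, all now Unlikely, the two without another explanation then become Possible and the two with one stay Unlikely. Typical events keep their present rating.
3. Say in the note whether ? admits a known answer, so that an event that recurs on re-exposure always has a row.
4. State that absence from the known reactions bears on expectedness, not on causality.
5. Reword the closing sentence so that treatment-related AEs are the sum of definite, probable and possible events, in line with sections 10.1 and 13.5.2.

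The cost is two table cells, a few sentences and a memo to sites. The treatment-related AE rate would rise slightly and a few more events would qualify for expedited review.
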